### Primary outcome measures

The co-primary effectiveness endpoints are the mean percent change in both forced expiratory volume in one second (FEV_1_) and distance traveled in the six minute walk test (6 MWT) in the treatment group (EBV implantation) as compared to the control group (optimal medical management) at 180 days after randomization. The primary safety endpoint is a comparison of major complications between the two groups over the initial follow-up period of 180 days. Additionally, patients will be followed for up to 3 years post randomization for long term safety assessment.

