#### Treatment group

The study group received the EBV implantation procedure within three weeks of randomization, and continued optimal medical management and exercise similar to the control group.

The goal of the implantation procedure was to completely isolate a single diseased lobe of the lungs by implanting EBV devices occluding all bronchial lumina leading to the targeted lobe. Bilateral treatment was not allowed in this study and acceptable target lobes did not include the right middle lobe. A single segmental airway not isolated by valves may allow ventilation to the lobe, thus reducing the potential benefit of the EBV devices. EBV devices were placed at the lobar, segmental, or sub segmental levels in this order of preference, depending on the anatomy of the patient noted at the time of the procedure.

The EBV implantation procedure was performed with the patient under general anesthesia and on a ventilator, or under moderate sedation with unassisted breathing. All patients were given antibiotics before and for 7 days following the procedure. Anesthesia was administered according to standard local protocols for bronchoscopy. For general anesthetic procedures, a rigid bronchoscope in conjunction with a flexible bronchoscope or a flexible bronchoscope alone through an endotracheal tube was allowed for valve placement.

Patients in both control and treatment arms were monitored for 1 year, with scheduled assessments at 1, 2–3, 7–10, 30, 90, 180, and 365 days post-procedure. Follow-up assessment includes the same variables as in the baseline assessment (see Table 2) with the primary outcome measures defined from the 180 ± 14 day follow-up visit.

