### Analysis

The power analysis is based on a pilot study in 38 patients in which FEV_1 _improved 14.9% ± 33.7 (mean ± SD) and 6 MWT distance improved 20.4% ± 41.5%. The samples size required to detect a 15% improvement in the treatment arm in FEV_1 _and a 17% improvement in 6 MWT distance at an alpha of 0.05 and a power of 0.90 is a minimum of 270 subjects with a 2:1 randomization to EBV procedure. Both of these values are above the threshold for minimal clinically important differences for these tests[17-19].

The study is designed as a superiority trial. For the two primary outcomes, the study is only considered a success if both endpoints show an improvement (one-sided test at p < 0.025). A one-sided test is appropriate to test for superiority. The actual probability of a false positive is lower than 0.025 given the imperfect correlation of the two endpoints. If change in FEV1 and change in 6 MWT were independent, the probability of a false positive would be 0.025*0.025 = 0.000625. In the pilot study generating the null hypothesis, the correlation coefficient between the change in FEV1 and 6 MWT was 0.3889. Given this r, the alpha for achieving a positive outcome is actually 0.005 (0.025*0.025^(1/(1+0.3889))). This is an assurance of avoiding a false positive well beyond convention.

The 2:1 randomization is chosen to enhance enrollment and increase the EBV population numbers in order to study covariates of treatment response. Although the 2:1 randomization increases the number of subjects required for the study, more robust subgroup comparisons may be possible.

For safety the 95% upper confidence interval for the Major Complication Composite rate delta between the EBV arm and the control arm is ≤ 30%.

The primary analysis cohort is intent to treat. As such, all 180 day missing data will be imputed using either a regression methodology if 30 and 90 day data are present or hot-deck imputation if there are not multiple datapoints available for a particular subject for regression analysis. Three unbiased imputations will be performed and the imputation resulting in the highest p-values will be selected as the final intent to treat dataset.

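### On a plain reading the 30-point safety limit is judged by intent to treat alone, where EBV patients who never have the procedure can mask the excess among those who do

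*Protocol article*

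**What the plan says.** All references are to the protocol article.

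- **Primary outcome measures:** "The primary safety endpoint is a comparison of major complications between the two groups over the initial follow-up period of 180 days". Safety is therefore a primary endpoint alongside FEV1 and six-minute walk.
- **Analysis, safety rule:** the requirement on the upper 95% confidence limit is that "the Major Complication Composite rate delta between the EBV arm and the control arm is ≤ 30" per cent. Whether the bound is one- or two-sided is not stated.
- **Analysis, next paragraph:** "The primary analysis cohort is intent to treat". It continues: "As such, all 180 day missing data will be imputed using either a regression methodology if 30 and 90 day data are present", with hot-deck imputation otherwise, and of three imputations "the imputation resulting in the highest p-values will be selected as the final intent to treat dataset".
- **Treatment group:** "The study group received the EBV implantation procedure within three weeks of randomization". The article does not say how many EBV patients were, or were expected to be, never implanted.
- **Sample size (Analysis):** "a minimum of 270 subjects with a 2:1 randomization to EBV procedure", that is, 180 EBV and 90 control.

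**The concern.** Intent to treat is the cautious choice for the two efficacy tests, because patients in the EBV arm without valves make superiority harder to show. The safety rule runs the other way. It is passed when a difference is shown not to be too large, so anything that draws the arms together helps it pass. Choosing the imputation with the highest p-values is likewise a safeguard for superiority tests and gives no protection for a confidence-limit rule.

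The article leaves room for dilution. Up to three weeks may separate randomisation from the procedure, in patients whose health it calls fragile and in whom it says exacerbations are frequent. Some EBV patients could withdraw or deteriorate in that window. They would count in the EBV denominator without any valve or procedure risk. At stake is whether a passed safety endpoint describes the excess faced by patients who actually have the procedure, which matters most when judging a device.

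**Working it through.** **The plan's own figure.** The article gives no power or sample-size figure for the safety rule. Its 270 is derived for efficacy, so there is nothing on the safety side to reproduce.

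**Inputs from the article.** n = 180 EBV and 90 control; limit 30 points.

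**Assumptions not in the article.** Control complication rate p0 = 5%, 10% or 20%; share u of the EBV arm never implanted, 0-10%; never-implanted patients at the control rate (varied in step 4); unpooled Wald limit.

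**Step 1: dilution.** EBV-arm rate p1 = (1 − u)(p0 + 0.30) + u·p0, so the arm difference is (1 − u) × 30 points. This is 28.5 points at u = 5% and 27 at u = 10%.

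**Step 2: an illustration.** Take 9/90 control events (10.0%) and 55/180 EBV events (30.6%).
- All randomised: difference 20.6 points; SE = √(0.3056 × 0.6944/180 + 0.10 × 0.90/90) = 0.0467; upper limit = 20.6 + 1.96 × 4.67 = 29.7. This passes.
- Suppose 18 EBV patients (10%) were never implanted and had 2 of those events. Implanted patients: 53/162 = 32.7%; difference 22.7 points; SE = √(0.3272 × 0.6728/162 + 0.001) = 0.0486; upper limit = 22.7 + 1.96 × 4.86 = 32.2. This fails.

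**Step 3: chance of passing when the true excess among implanted patients is exactly 30 points.** Sum the probabilities of all outcomes of Bin(180, p1) and Bin(90, p0) with difference + z·SE ≤ 0.30.

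| Limit | Control rate | u = 0 | u = 2% | u = 5% | u = 10% |
|---|---|---|---|---|---|
| Two-sided 95% (z = 1.96) | 5% | 2.2% | 3.1% | 5.0% | 10.2% |
| | 10% | 2.1% | 2.8% | 4.3% | 8.1% |
| | 20% | 2.1% | 2.7% | 3.8% | 6.8% |
| One-sided 95% (z = 1.645) | 5% | 4.7% | 6.3% | 9.5% | 17.4% |
| | 10% | 4.5% | 5.9% | 8.5% | 14.7% |
| | 20% | 4.5% | 5.6% | 7.7% | 12.4% |

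**Step 4: never-implanted patients at higher risk.** Two-sided limit, control rate 5%:

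| Their complication rate | u = 5% | u = 10% |
|---|---|---|
| 5% (control rate) | 5.0% | 10.2% |
| 20% | 3.4% | 5.0% |
| 30% | 2.5% | 2.9% |
| 35% (same as implanted) | 2.2% | 2.2% |
| 40% | 1.9% | 1.6% |

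**Step 5: implanted EBV patients versus all controls.** With the two-sided limit and u = 5-20%, the chance of passing at a true 30-point excess among implanted patients is 2.1-2.4% at all three control rates. Requiring both sets to pass cannot raise it above that, whatever the risk of the never-implanted.

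**Step 6: far from the limit.** With a true excess of 10 points among implanted patients and a 10% control rate, the intent-to-treat rule passes at least 99.8% of the time at every u. The choice of cohort matters only when the true excess is near the limit.

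**The case against.** **No sentence ties intent to treat to the safety rule.** A reader might infer that the article states the link. It does not. The safety rule is a paragraph of its own, and the text after the cohort sentence is about imputing 180-day measurements and comparing p-values, which is efficacy language. A safety set may be defined in the full protocol or analysis plan, and its absence from a condensed article is not a fault. This stands, so the point rests on the plain reading that a primary endpoint is judged in the only primary cohort named.

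**The error rate of the stated rule is not inflated.** A reader might call the figures above a raised false-pass rate. The article's limit applies to the difference between arms, and when that difference is truly 30 points the chance of passing stays at about 2.1-2.2% (two-sided limit). At u = 10% the arm difference is 27 points, which is inside the limit. The figures describe a different quantity, the excess among patients exposed to the procedure. This stands.

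**The size rests on outside assumptions.** Eligibility is confirmed after rehabilitation, just before randomisation, which limits late unfitness, and the article says the study group received the procedure. Patients who drop out because they became unfit may have more complications than controls, and step 4 shows that the effect then shrinks or reverses. This stands too.

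**The limit is not the only safeguard.** A reader might take it as the sole check on risk. The Overview provides safety stopping rules set by the DSMB and committee adjudication of relatedness to valve or procedure, and Table 1 lists device-related events as secondary safety endpoints.

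**An implanted-only comparison drops patients from one arm and can be the more favourable of the two.** That is a good reason not to use it alone. It does not count against requiring both.

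**Conclusion.** The concern holds in a limited form. On its plain reading, the article judges a not-too-much-worse rule in the intent-to-treat cohort alone. In that cohort, EBV patients who never have the procedure can bring the limit within reach although the excess among exposed patients is 30 points.

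With the two-sided limit, control rates of 5-20% and never-implanted patients at the control rate, the chance of passing rises from about 2.1-2.2% to 2.7-3.1% at 2% not implanted, 3.8-5.0% at 5% and 6.8-10.2% at 10%. With none missing there is no effect. The issue is material only if roughly 5-10% or more are never implanted, they carry low risk, and the true excess is near the limit.

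The documents do not show that dilution occurred, and they do not make intent to treat wrong in itself, since it preserves the randomised comparison. The change is worth making because it is cheap and removes the doubt.

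**What to change.** State the cohort for the safety rule. Require the upper limit of at most 30 points to hold in both:

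1. all randomised patients, by assigned arm; and
2. EBV patients in whom the procedure was started, versus all controls.

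Claim the safety endpoint only if both meet it. Keep intent to treat for the efficacy tests.

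The cost is one more table from data already collected. The second comparison is not strictly as randomised and may be more or less favourable than intent to treat. The rule is also harder to pass when non-receipt is common: at a true excess of 20 points among implanted patients, a 10% control rate and 10% not implanted (at the control rate), the two-sided limit is met 75.2% of the time by intent to treat and 55.3% in the second set. With everyone implanted the figure is 57.8%, so most of what is lost is the advantage that dilution gave. If nearly all EBV patients have the procedure, the two results will be close and little is lost.

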### Secondary outcome measures

Disease specific quality of life (as measured by St. George's Respiratory Questionnaire), exercise capacity as measured by incremental cycle ergometry, daily supplemental oxygen requirement, and dyspnea (as measured by the modified Medical Research Council (mMRC) dyspnea scale, (see Table 1) are secondary efficacy endpoints to be assessed at baseline and 180 days post randomization. Appropriate adjustments will be made to account for impact on Type I error[11].

**Table 1 T1:** Outcome measures

**Co-primary efficacy endpoints**	Mean % change in FEV_1 _and 6 MWT in the treatment group as compared to control group at 180 days post randomization.
**Primary safety endpoint**	Major Complications Composite at 180 days post randomization.
**Secondary efficacy endpoints**	Mean absolute change in: - St. George's Respiratory Questionnaire - Maximal work load as measured by cycle ergometry - Daily oxygen requirement - mMRC
**Secondary safety endpoints**	Complications (type, timing, and severity, including Kaplan-Meier survival analysis) Device-related adverse events during procedure hospitalization Device-related adverse events post discharge

Abbreviations: FEV_1 _= forced expiratory volume in one second, 6 MWT = six minute walk test, RV = residual volume, DLco = diffusion of the lung for carbon dioxide, BODE index = body-mass index, airflow obstruction, dyspnea, and exercise capacity index, EBV = endobronchial valve, mMRC = modified Medical Research Council dyspnea scale

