The initial analysis will evaluate the mean percent change between EBV and control in FEV_1 _and 6 MWT using an unpaired t-test if data are normally distributed or Mann-Whitney-Wilcoxon test if data require non-parametric testing. To determine if covariates impact the primary outcome variables, and to adjust for potential imbalances in randomization, both primary endpoints will be further tested via a multivariate model (SAS PROC MIXED). In order to reduce the possibility of over-specification of the model, the potential covariates listed in Tables 6, 7, 8, 9 will be subjected to a univariate screening procedure similar to that described by Hosmer and Lemeshow[20]. Derivations for these variables are provided in Table 10. Main effects and interactions with a p-value of 0.15 or less are allowed to enter a multivariate analysis using a mixed linear model (SAS PROC MIXED). The treatment effect must remain in the model in order to substantiate the one-tailed test of superiority. Those variables found to have statistically significant interactions with the treatment arm via the mixed model analysis will be further analyzed in follow-on sub-group analyses. In order to limit the impact of multiple hypothesis testing, univariate sub-set analysis will be performed using only those independent variables that remain in the mixed model as interactions with the treatment arm. For those analyses performed on the remaining independent variables, appropriate adjustments will be made to account for impact on Type I error[11]. Secondary endpoint analyses will follow the same methodology as described above.

**Table 6 T6:** Plethysmography, spirometry and HRCT derived baseline potential covariates*

Variable	Plethysmography/Spirometry	HRCT at TLC	HRCT at RV	TLC and RV HRCT ^†^
RV	X			
RV % Predicted	X			
TLC	X			
TLC % Predicted	X			
RV/TLC	X			
VC	X			
FVC	X			
FVC % Predicted	X			
FEV_1_	X			
FEV_1 _% Predicted	X			
FEV_1_/FVC	X			
Destruction Score of Target Lobe		X	X	
Ipsilateral Heterogeneity^††^		X	X	
Whole Lung Heterogeneity^††^		X	X	
For RUL Treatment Subset only: RUL-RML Heterogeneity^††^		X	X	
Target Lobe Volume % of TLC		X		
Target Lobe Volume % of RV			X	
Max Destruction Score other than target		X	X	
Min Destruction Score other than target		X	X	
Target Lobe Destruction Score % TLC-RV Delta				X
Target Lobe Volume % TLC-RV Delta				X
Fissure Score^†††^		X		

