Advanced emphysema is characterized by destruction of lung parenchyma and augmentation of anatomic connections for air passage between adjacent lung lobules. Unfortunately for endobronchial lung volume reduction procedures, these collateral communications may traverse lobar fissures [25]. These peripheral communications between lobes then may allow for continued lobar ventilation despite completely occluded lobar airways. Because this collateral ventilation is not easily quantified by current detection methods, the outcome of EBV valve placement may be heterogeneous. Ultimately, secondary analyses will include responder analysis, in order to determine the proportion of patients with clinically meaningful responses.

Given the complex mechanical and gas exchange consequences of valve insertion, it is possible that the magnitude of volume reduction in a lobe may not be associated with changes in other meaningful physiologic or functional indices following the procedure. For example, the impact of valve placement on symptoms associated with dynamic hyperinflation or variations in gas exchange utilizing collateral channels may be associated with clinical improvements independent of changes in conventional resting pulmonary tests. The composite primary endpoint was chosen to include a functional exercise measure to capture such changes.

Ultimately, the future of the EBV valve will be determined by the balance between efficacy and safety. Since the valves are removable for mild or moderate adverse events, valve safety will be impacted by the frequency of severe adverse events that might affect survival in a compromised patient population. In fact, individuals who demonstrate improvements in lung function may also demonstrate an increase in exacerbation frequency. For this reason, quality of life indices including the Quality of Well Being Scale and the Saint George's Respiratory Questionnaire are considered integrative parameters which can determine the balanced impact of the intervention [26,27]. One strategy to minimize overall adverse response would be to remove valves earlier in the patients who do not have clinically important responses. If a meaningful outcome is measurable in the first few days after the procedure, future alternative targeting strategies might be employed to determine response at earlier times after randomization.

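### As worded, the day-180 imputation rule covers patients who have died, so deaths would enter both co-primary analyses with values derived from survivors

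*Protocol article*

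**What the plan says.** The Analysis section states "The primary analysis cohort is intent to treat" and derives the missing-data rule from that choice: "all 180 day missing data will be imputed using either a regression methodology if 30 and 90 day data are present", or else "hot-deck imputation if there are not multiple datapoints available for a particular subject for regression analysis". It then adds: "Three unbiased imputations will be performed and the imputation resulting in the highest p-values will be selected as the final intent to treat dataset".

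The endpoint time is fixed under Treatment group, "with the primary outcome measures defined from the 180 ± 14 day follow-up visit". The arms are compared on percent change "using an unpaired t-test if data are normally distributed or Mann-Whitney-Wilcoxon test if data require non-parametric testing".

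Survival appears on the safety side only. Table 1 lists among the secondary safety endpoints "Complications (type, timing, and severity, including Kaplan-Meier survival analysis"). Nothing in the article exempts deaths from the imputation rule, gives them a worst value or rank, or combines death with either co-primary endpoint.

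**The concern.** A patient who has died has no day-180 FEV1 or walking distance to recover, so death differs in kind from a missed visit. The published rule does not separate the two. A patient who dies on day 120 after good day-30 and day-90 visits falls under the regression branch and could be counted as improved on both co-primaries. A patient who dies in the first weeks falls under the hot-deck branch, and the donor must be someone who was measured at day 180.

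Only one arm undergoes a procedure, so unequal early mortality is possible. The Discussion says that "valve safety will be impacted by the frequency of severe adverse events that might affect survival in a compromised patient population" and that the valve's future rests on weighing efficacy against safety. If EBV deaths exceeded control deaths, the efficacy side of that balance would not register them, and the estimate would be too favourable.

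**Working it through.** **What the rule does with a death.** The cohort is intent to treat, so a deceased patient stays in. The rule covers all missing day-180 data, so the patient receives a value.

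- Regression branch: a model for day 180 is naturally fitted to patients measured at day 180, that is, survivors. If the patient's own visits were extrapolated instead, the result would still be a day-180 measurement for someone who has none.
- Hot-deck branch: the donor is a survivor.
- Taking the highest p-value of three imputations does not remove the problem, because all three give the deceased a living patient's value.

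**Inputs from the Analysis section.** Effects are 15% (FEV1) and 17% (walk). Pilot SDs are 33.7 and 41.5. A minimum of 270 patients at 2:1 gives 180 EBV and 90 control. Each endpoint is tested one-sided at 0.025.

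**Assumptions, not in the article.** Mortality to day 180 is pE (EBV) and pC (control). Survivor mean changes are 15 or 17 points (EBV) and 0 (control). Imputation gives deaths their arm's mean. The comparator scores a death as −100% change.

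**Formulae.** With imputation at the arm mean, the expected difference stays at 15 (FEV1) or 17 (walk) whatever the mortality. With death at −100%:

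- FEV1 difference = (1 − pE) × 15 − 100 pE + 100 pC, so the reduction is 115 pE − 100 pC
- Walk difference = (1 − pE) × 17 − 100 pE + 100 pC, so the reduction is 117 pE − 100 pC

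| Deaths EBV / control | FEV1 difference | Reduction from 15 | Walk difference | Reduction from 17 |
|---|---|---|---|---|
| 3% / 3% | 14.55 − 3 + 3 = 14.55 | 0.45 | 16.49 | 0.51 |
| 3% / 1% | 14.55 − 3 + 1 = 12.55 | 2.45 | 14.49 | 2.51 |
| 5% / 1% | 14.25 − 5 + 1 = 10.25 | 4.75 | 12.15 | 4.85 |

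In patients, 3% of 180 is about 5 EBV deaths and 5% is 9.

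**Direction.** Each EBV death is worth 115/180 = 0.64 FEV1 points, and each control death 100/90 = 1.11 points the other way. With equal mortality from 1% to 5% the FEV1 reduction is 0.15 to 0.75 points. If control mortality exceeded 1.15 times EBV mortality, the sign would reverse and the rule would work against the valve.

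**Effect on power.** The article gives no figure for this point. With 180 and 90 patients and no deaths, normal-approximation power is 93% (FEV1) and 89% (walk). At 5% / 2% deaths:

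| Analysis | FEV1 power | Walk power |
|---|---|---|
| t-type test, deaths at −100% | 93% → 63% | 89% → 62% |
| Mann-Whitney-Wilcoxon, deaths ranked worst (2,000 simulated trials) | 92% → 79% | 88% → 71% |

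The rank analysis loses less because a death is a lowest rank and not an extreme value in a mean.

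**The case against.** The strongest reply is that the rule never mentions death. If death is not a missing measurement, a rule about missing data may simply be silent on it, and a condensed article may leave the handling of deaths to the full protocol or analysis plan. This limits the claim but does not remove it. The published rule says all, ties this to the intent-to-treat cohort, and would be applied to deaths by anyone following it as written. Whether the full documents contain a separate rule for deaths is unknown.

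A reader might infer that the article documents substantial early mortality. It does not. The Discussion says only that severe events might affect survival. The pilot figure of 6.1% at 90 days is for pneumothorax, and the mortality cited from the surgical trial is two-year mortality in a subgroup.

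A reader might also infer that efficacy would be overstated by exactly the patients harmed. That is too strong. Regression on day-30 and day-90 values would carry forward a decline already measured. The hot-deck donor pool is not described, and pooling donors across arms would pull the EBV mean towards control. The −100% score is a convention, and the rule applies to both arms.

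Nor does the plan ignore deaths: there is a Kaplan-Meier analysis, a 180-day comparison of major complications, event adjudication and a DSMB. Assessing survival separately from lung function is a legitimate choice. These provisions do not change the efficacy estimate, however. The safety criterion allows an upper confidence limit of 30% on the difference in complication rates, so a mortality excess of a few points need not show there.

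**Conclusion.** The concern holds as a defect in the stated rule. Followed literally, the rule gives patients who die before day 180 a survivor-derived value in both co-primary analyses, and the estimate is too favourable if deaths are more frequent in the EBV arm.

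The size is unknown because no mortality rate is given. The illustrated FEV1 shifts of about 0.5 to 4.8 points rest on three assumptions: the death rates, imputation at the arm mean, and a −100% score for death. They contrast two ways of defining the outcome and do not estimate a bias known to be present. Material distortion needs excess EBV deaths. The documents do not support saying that such an excess exists or that the efficacy conclusion is wrong.

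**What to change.** - Limit the regression and hot-deck rule to patients alive at day 180 who lack a measurement.
- Keep deaths in the intent-to-treat comparison through a pre-specified worst-rank Mann-Whitney-Wilcoxon analysis of both co-primaries, with every death ranked below all survivors. The Analysis section already names this test.
- Report it as a key sensitivity analysis and not as an extra condition for success. The trial must already succeed on two endpoints, and the power figures above show what a further gate could cost.
- Report deaths by arm beside the co-primary results.

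The plan should also state that the comparison of mean changes then describes patients alive at day 180, while the worst-rank analysis covers deaths as well. Under the arm-mean assumption, leaving deaths out of the mean comparison still gives an expected difference of 15 points. Restricting imputation therefore makes the estimate honest about whom it describes, and the worst-rank analysis and the death counts supply the missing information.

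The cost is one more analysis and a short change to the text. If EBV deaths exceed control deaths, that analysis will give a less favourable efficacy result with lower power.

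### The day-180 imputation rule makes no stated use of a patient's only early result, and bias follows if response-related loss differs between arms

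*Protocol article*

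**What the plan says.** All references are to the protocol article.

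- **Primary dataset (Analysis).** "The primary analysis cohort is intent to treat". Missing day-180 values are "imputed using either a regression methodology if 30 and 90 day data are present or hot-deck imputation if there are not multiple datapoints available". The end of that sentence makes the hot-deck condition patient by patient: it turns on whether there are "multiple datapoints available for a particular subject for regression analysis".
- **Selection among imputations (Analysis).** "Three unbiased imputations will be performed and the imputation resulting in the highest p-values will be selected as the final intent to treat dataset".
- **Visits (Treatment group).** Both arms have "scheduled assessments at 1, 2–3, 7–10, 30, 90, 180, and 365 days post-procedure". "Follow-up assessment includes the same variables as in the baseline assessment", and the baseline list in Table 2 includes spirometry and the 6 MWT. The endpoint is read at day 180: "primary outcome measures defined from the 180 ± 14 day follow-up visit".

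The article gives no donor rule for the hot-deck (matched or unmatched, within arm or pooled), no expected dropout rate, and no correlation between early and day-180 change.

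**The concern.** FEV1 and 6 MWT are scheduled at both day 30 and day 90, so a patient can reach day 180 missing with exactly one early result: by leaving between the two visits, or by missing one visit and later leaving. Whether that patient's result informs the imputed day-180 value depends on attendance at a second visit, which is not a sound reason to set aside a measured outcome.

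The two conditions are also not complements. Baseline plus one follow-up visit is arguably more than one datapoint, yet it does not meet the requirement for both day 30 and day 90. The same patient could be put in either branch, and in an open-label trial that choice could be made with results in view.

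The plan calls the imputations unbiased. For one-visit patients under unmatched hot-deck, that holds only if leaving is unrelated to early response. Only one arm receives a procedure and a removable device, and the Study limitations section accepts that knowledge of assignment may affect exercise measurements and the interpretation of events. Loss that depends on response and differs between arms is therefore plausible, though the article does not document it. Both co-primary endpoints pass through this rule.

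**Working it through.** The plan attaches no figure to this rule, so there is none to reproduce.

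**1. Which branch applies when day 180 is missing**

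| Early values present | Branch on the plain reading | Early result used? |
|---|---|---|
| Day 30 and day 90 | Regression | Yes |
| Day 30 only | Hot-deck (wording arguable) | Not by the stated rule |
| Day 90 only | Hot-deck (wording arguable) | Not by the stated rule |
| Neither | Hot-deck | None to use |

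**2. Inputs**

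From the Analysis section: at least 270 patients at 2:1, hence 180 and 90; FEV1 SD 33.7; effect 15 points; one-sided 0.025; three imputations with the highest p-value kept. Assumed: correlation r between early and day-180 change of 0.5 to 0.7; 5% to 15% of an arm with day 180 missing and one early value; unmatched donors within arm.

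**3. One record**

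Take an EBV patient with FEV1 down 20% at the only early visit, and assume the early arm mean and SD equal those at day 180.

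- Unmatched within-arm hot-deck: expected value +15 if completers average the planned effect.
- Regression on the one value: 15 + r × (−20 − 15), which is −2.5 at r = 0.5 and −9.5 at r = 0.7.
- Gap: 17.5 to 24.5 points for this patient.

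**4. Effect on the treatment difference, single imputation**

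Bias ≈ (EBV share × EBV gap) − (control share × control gap), where the gap is the completers' mean minus the true mean of the one-visit patients. Losses here are drawn from the worse half on the early value in both arms. The simulated EBV gap was 14.2 to 15.9 points at r = 0.5 and 19.5 to 21.7 at r = 0.7.

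Hand check at 10% EBV and 5% control, using the 5% gap for control (5% of 90 is taken as 4 patients, 4/90 = 4.4%):

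- r = 0.5: 0.10 × 14.9 − 0.044 × 14.2 = 1.49 − 0.63 = 0.86 (simulated +0.85).
- r = 0.7: 0.10 × 20.9 − 0.044 × 19.5 = 2.09 − 0.87 = 1.22 (simulated +1.22).

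| Loss EBV / control | Unmatched within-arm hot-deck, bias in points |
|---|---|
| 5% / 5% and 10% / 10% | −0.05 to +0.2 |
| 10% / 5% | +0.9 to +1.2 |
| 15% / 5% | +1.8 to +2.4 |
| 5% / 10% | −0.7 to −1.1 |
| 5% / 15% | −1.7 to −2.4 |

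Donors pooled over arms gave −4.0 to +0.9. Regression on the one value left at most 0.1 point, and hot-deck matched on it at most 0.25.

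**5. With the highest-p-of-three rule, true FEV1 effect zero**

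The rule is applied to FEV1. In the selective rows, EBV losses are mainly the poorest early responders and control losses are random.

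| Setting | Bias, points | FEV1 one-sided rejection (nominal 0.025) |
|---|---|---|
| 5% selective loss in EBV | about +0.8 to +1.6 | about 0.04 to 0.065 |
| 10% selective loss in EBV | about +1.7 to +3.2 | 0.07 to 0.14 |
| Same selection and rate in both arms | −0.5 to −1.1 | about 0.02 to 0.03 |
| Random missingness | not directional before selection | below 0.025 |
| Selective loss, one early value used by regression | no selective bias | about 0.02 |

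The negative bias in the third row comes from keeping the least favourable of three imputations, since a single imputation gives about nil there.

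**The case against.** **Donor selection may be specified elsewhere.** A condensed article can leave donor classes to the full protocol or SAP, and hot-deck matched on the early value would remove nearly all of the bias. This stands against any claim that the plan specifies random donors. It does not dispose of the branching rule, which the article itself states and which makes no use of the single value.

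**The highest-p-of-three rule is conservative.** This stands in part. With random missingness it keeps the FEV1 rate below 0.025, so no inflation should be claimed there. With selective loss in EBV it roughly halves the excess at 5% but does not remove it.

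**The harmful scenario is chosen for its direction.** This is fair. Equal, symmetric loss gives about nil, more loss of poor responders in control works against the valve, and the article gives no dropout pattern.

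**Success needs both endpoints.** This is correct: the rates above are for FEV1 alone and are not the trial's false-positive rate.

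A reader might also infer that measured day-30 or day-90 results are overwritten, or that failing patients in general are scored as average. The text supports neither. Only the missing day-180 value is filled, the 30- and 90-day results are still collected and reported, and patients with both early values go to regression.

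**Conclusion.** The point holds in a limited form. As stated, the rule imputes one-visit patients without use of their measured early result, and its two conditions leave their branch open to argument. The description "Three unbiased imputations will be performed" is justified for these patients only if leaving is unrelated to early response or donors are matched on it.

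The consequence is conditional. It requires response-related loss that differs between arms (or donors pooled over arms), and its direction depends on which arm loses more poor responders. Under the assumptions shown, selective loss of 5% to 10% of the EBV arm shifts the FEV1 difference by about 0.8 to 3.2 points. That is 5% to 21% of the 15-point target (0.8/15 and 3.2/15), with an FEV1 rejection rate of about 0.04 to 0.14. The loss shares, the correlation and the unmatched donors are assumptions, so these figures illustrate what could happen and do not forecast it. The change is worth making because a better rule costs almost nothing.

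**What to change.** Replace the two-branch rule with one model. Impute day 180 by regression on arm, baseline value, randomisation strata and any available day-30 or day-90 value. Alternatively, fit PROC MIXED, which the plan already names, to the day 30, 90 and 180 values by arm. Keep hot-deck only for patients with no post-baseline value, and draw their donors from the same arm and stratum.

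The cost is a wording change in the Analysis section and a few lines of code, with no new data or patients. The downside is small: one-visit patients would rely on a missing-at-random model, which the plan already accepts for two-visit patients.
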